### Interventions

For this study, the bilateral Hegu (LI4), Neiguan (P6), Zusanli (ST36), and Sanyinjiao (SP6) acupoints will be selected. A HANS 100B (four conductors, eight electrodes) transdermal acupoint electrical stimulation apparatus (Nanjing Jisheng Company) will be used to stimulate the bilateral Hegu (LI4) and Neiguan (P6) acupoints for 30 min before anesthetic induction and during the intraoperative period until suturing of the surgical site is completed. The Hegu (LI4), Neiguan (P6), Zusanli (ST36), and Sanyinjiao (SP6) acupoints will be stimulated at 9:00 a.m. and 3:00 p.m. each day on the 1st, 2nd, and 3rd postoperative days. Each treatment will last for 30 min. Stimulation parameters will be as follows: a dense-disperse frequency of 2/100 Hz, with true stimulation being the maximum tolerable setting for a patient, and with sham simulation being 1 mA lower than the current that patients are able to just feel. The test groups for Part 1 are presented in Table 1, and a study design flowchart is shown in Fig. 1.

**Table 1 Tab1:** Part 1 test groups

Group	Sample size (*n*)	Intervention
Con	80	Sham TEAS before, during, and after operation
T1	120	Preoperative and intraoperative TEAS, and postoperative sham TEAS
T2	80	Preoperative TEAS, intraoperative sham TEAS, and postoperative TEAS
T3	120	TEAS before, during, and after operation

*TEAS* transcutaneous electrical acupoint stimulation

**Fig. 1 Fig1:**
[figure not shown]
Part 1 trial flowchart. For group details, see Table 1. d days, TEAS transcutaneous electrical acupoint stimulation

Preliminary data analysis based on Part 1 suggest potential benefits of postoperative TEAS for gastrointestinal function recovery, but the effect was slight. Previous animal experiments have suggested that 5 Hz is more effective than 2/100 Hz as a means of promoting the recovery of gastrointestinal function, so we will adjust the study stimulation frequency before initiating Part 2 of this study protocol. In Part 2, all patients will be stimulated at 2/100 Hz (Hegu (LI4) and Neiguan (P6) acupoints; bilateral) before and during surgery. After surgery, patients will receive no TEAS, sham TEAS, 5-Hz TEAS, or 100-Hz TEAS. The same acupoints will be assessed in this trial. In order to observe colorectal function recovery more specifically, Part 2 of this study will focus only on patients undergoing colorectal surgery. The test groups for Part 2 of this study are presented in Table 2, with a study design flowchart shown in Fig. 2.

**Table 2 Tab2:** Part 2 test groups

Group	Sample size (*n*)	Intervention		
		Preoperative	Intraoperative	Postoperative
Con′	100	2/100 Hz TEAS	2/100 Hz TEAS	Control
T1′	100	2/100 Hz TEAS	2/100 Hz TEAS	Sham TEAS
T2′	100	2/100 Hz TEAS	2/100 Hz TEAS	5 Hz TEAS
T3′	100	2/100 Hz TEAS	2/100 Hz TEAS	100 Hz TEAS

*TEAS* transcutaneous electrical acupoint stimulation

**Fig. 2 Fig2:**
[figure not shown]
Part 2 study design flowchart. For group details, see Table 2. d days, TEAS transcutaneous electrical acupoint stimulation

Anesthesia protocols will be identical in Part 1 and Part 2 of this study, with midazolam (0.03 mg/kg), propofol (1.5–2.5 mg/kg), sufentanil (0.3–0.4μg/kg), and rocuronium (0.8 mg/kg) used to achieve effective anesthesia, and with patients undergoing mechanical ventilation after tracheal intubation. Anesthesia maintenance during the intraoperative period will be achieved using remifentanil (0.05–0.2 μg/kg/min), propofol, and rocuronium. Sedation depth will be monitored according to the Bispectral Index (BIS), maintaining BIS values between 45 and 55 by adjusting the propofol infusion rate, and adjusting respiratory parameters to maintain a PetCO_2_ of 35-45 mmHg. If a patient’s heart rate (HR) falls below 50 bpm or to 30% below baseline, they will be given 0.25–0.5 mg atropine; if their HR rises to above 100 bpm or to more than 30% above baseline, esmolol (0.2–0.5 mg/kg) will be given as appropriate. If blood pressure falls to < 90/60 mmHg or to below 30% of baseline, 6 mg ephedrine will be administered to maintain hemodynamic stability. Sufentanil (5–10 μg) or 0.05 mg fentanyl will be given as appropriate following peritoneal suturing, and a prophylactic long-acting 5-HT_3_ receptor antagonist will be used. Patients will be connected with a PCIA pump (250 μg sufentanil plus saline to a total volume of 250 ml; 1 ml/h, 3 ml/bolus, 10-min interval). After skin suturing, sedative and analgesic drug administration will be terminated, and patients will be transferred to a post-anesthesia care unit (PACU). After patients resume spontaneous breathing, muscle relaxation antagonists (neostigmine 1–2 mg, atropine 0.5–1 mg, and flumazenil 0.5 mg, if necessary) will be given, and the extubation time will be recorded. Once the patient is fully awake, pain scores will be assessed and adverse events recorded.

GCP-trained nurses will check the bowel sounds by auscultation of the patients’ left lower abdomen or right lower abdomen at 3:00 a.m., 9:00 a.m., 3:00 p.m., and 9:00 p.m. each day on the 1st, 2nd, and 3rd postoperative days. Each auscultation will last for 3 min.

Patients and their families will be taught how to record postoperative diaries before study initiation, including time of water intake, solid food tolerance, first anal exhaust, and the time at which the patient is first able to leave bed. These diaries will be returned to researchers on the 5th day after operation.

Analgesics will be administered as follows: when the pain NRS score is ≥ 4 even after five consecutive effective bolus applications of the PCIA pump, 50 mg pethidine will be given intramuscularly.

PONV will be treated as follows: nausea levels will be scored via NRS (0–10; 0 for no nausea, 10 for intolerable nausea). 5-HT_3_ receptor antagonists will be given for nausea scores ≥ 7 or when patients vomit more than once. Rescue medication including pethidine and 5-HT_3_ receptor antagonists will be recorded in the remedial tables.

Venous blood (5 ml) will be collected both at the preoperative stage prior to TEAS and 4–5 days after operation. The blood samples will be sent to the Department of Immunology of Peking University Medical Department for immunological and inflammatory index measurements.

When an adverse event occurs, the observer will be able to decide whether to discontinue the observation based on the patient’s condition. If serious adverse events occur, the researchers will immediately take necessary measures to ensure the safety of the patients. All adverse events will be tracked and carefully recorded until the subjects are stable. Those with abnormal laboratory examinations of clinical significance will be monitored until readings return to pretreatment levels.

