#### Secondary outcomes

##### Postoperative recovery of gastrointestinal function

Measured variables for this outcome include: water intake time (the time of first water intake after operation), solid food tolerance time (solid food tolerance indicates that there is no nausea or vomiting within 4 h after a meal), first anal exhaust time, the time at which the patient is able to leave the bed, and the use of gastrointestinal functional adjuvant medicines.

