##### Quality of life assessment

The SF-8 questionnaire will be used to assess quality of life before the operation and 1 month after discharge.

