### Statistical analysis

Continuous variables will be expressed as: mean (SD), median (interquartile range (IQR)), or minimum and maximum. For comparisons between treatment groups, analyses of variance (ANOVAs) will be used for normally distributed variables, and the Kruskal–Wallis *H* test will be used for non-normally distributed variables. Categorical variables will be expressed as numbers (%), and will be analyzed via chi-square tests for between-group comparisons.

Statistical significance for this study is defined as α = 0.05 for a two-sided test. *P* values will be rounded to three decimal places; values below 0.001 will be reported as < 0.001. Statistical analyses will be conducted using SAS version 9.4 (SAS Institute Inc.).

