### Missing data

Missing primary endpoint data will be imputed using the last-observation-carried-forward (LOCF) method. In cases of missing baseline data, the mean of all patients will be used for imputation. Missing data for other observations will not be imputed.

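### Diary-based recovery times stop at day 5, and the stated missing-data rule and methods leave patients who have not reached a milestone without a usable time; this can bias the comparison, mainly for solid food tolerance

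*Protocol article*

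**What the plan says.** The Interventions section describes a diary kept by patients and families, "including time of water intake, solid food tolerance, first anal exhaust, and the time at which the patient is first able to leave bed". It fixes the collection day: "These diaries will be returned to researchers on the 5th day after operation". No clock time is given.

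These four times make up most of the first secondary outcome, postoperative recovery of gastrointestinal function. One of them has a demanding definition: "solid food tolerance indicates that there is no nausea or vomiting within 4 h after a meal".

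The Missing data section has separate rules. For the primary endpoint, "Missing primary endpoint data will be imputed using the last-observation-carried-forward (LOCF) method". Missing baseline values get the overall mean. For everything else, "Missing data for other observations will not be imputed".

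Under Statistical analysis, "analyses of variance (ANOVAs) will be used for normally distributed variables", with Kruskal–Wallis otherwise. The section on primary and secondary efficacy endpoints adds an ANCOVA, and a CMH test for ordinal and categorical variables.

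The only later contact described is for quality of life: "The SF-8 questionnaire will be used to assess quality of life before the operation and 1 month after discharge". No milestone question is attached to it.

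**The concern.** Each rule is ordinary taken alone. Together they create a gap. A patient who has not reached a milestone when the diary is handed in has no time to enter. The stated rule supplies no value, and each named method for continuous outcomes needs a complete value for every patient analysed. The natural result is that the patient is left out of that comparison.

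Whether a time is absent then depends on how long it is. The comparison is made among patients who recovered before day 5, not among all those randomised, and the share removed can differ between arms. The slowest recoveries, which say most about a treatment meant to speed bowel function, contribute nothing.

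Solid food tolerance is the most exposed milestone, since it needs a meal followed by 4 h free of nausea and vomiting. The protocol also scores nausea through day 5, so it allows for symptoms lasting that long.

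**Working it through.** **The plan's own figure.** The sample size section gives a difference of 8.762 h in bowel-sound time, SD 17.8 h, 3:2 allocation and 90% power; the Statistical analysis section gives two-sided 0.05. The smaller group is (1 + 1/1.5) × [17.8 × (1.960 + 1.282) / 8.762]² = 72.3, so 73, and 1.5 × 73 = 109.5, so 110. This matches the stated 73 and 110. After 10% dropout from 80 and 120, 72 and 108 remain, with t-test power 0.896.

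**What must be assumed.** No mean, SD or late share is given for any diary time. I borrow the 8.762 h difference and the 17.8 h SD from bowel sounds, assume normal times, vary the control mean, and set the cut-off c at 120 h.

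**Formulas.** With a = (c − μ)/σ:
- share without a recorded time = 1 − Φ(a)
- mean of recorded times = μ − σ·φ(a)/Φ(a)
- variance of recorded times = σ²[1 − aλ − λ²], with λ = φ(a)/Φ(a)

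Power is for a two-sided t-test with 72 and 108 patients, less those lost.

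**Worked case, control mean 96 h.**
- Control: a = 24/17.8 = 1.348, λ = 0.1607/0.9112 = 0.1764, recorded mean 96 − 17.8 × 0.1764 = 92.86 h.
- TEAS, mean 87.238 h: a = 1.841, λ = 0.0733/0.9672 = 0.0758, recorded mean 87.238 − 17.8 × 0.0758 = 85.89 h.
- Recorded difference: 6.97 h.

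**Equal SD 17.8 h, cut-off 120 h**

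| Control mean (h) | Lost, control | Lost, TEAS | Recorded difference (h) | Power |
|---|---|---|---|---|
| 60.3 | 0.04% | 0.01% | 8.74 | 0.895 |
| 84 | 2.2% | 0.6% | 8.13 | 0.866 |
| 96 | 8.9% | 3.3% | 6.97 | 0.786 |
| 108 | 25.0% | 12.2% | 5.31 | 0.594 |

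From 84 h down, the attenuation is 7%, 20% and 39% of 8.762 h.

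**Earlier cut-off.** Since day 5 has no clock time, the effective cut-off may fall before 120 h. At 108 h, a control mean of 96 h already gives 5.31 h. At 96 h, even a mean of 60.3 h loses 2.3% of controls and gives 8.10 h.

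**Pilot SDs as reported (sham 9.8167 h, TEAS 17.8499 h), cut-off 120 h**

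| Control mean (h) | Lost, control | Lost, TEAS | Recorded difference (h) |
|---|---|---|---|
| 60.3 | <0.01% | 0.01% | 8.77 |
| 84 | 0.01% | 0.6% | 9.07 |
| 96 | 0.7% | 3.3% | 9.93 |
| 108 | 11.1% | 12.2% | 10.80 |

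Here TEAS has the wider spread and loses more patients from its upper tail, so the difference grows.

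**The case against.** The strongest reply is that much of this rests on silence. The article says when the diary is returned. It does not say that outstanding milestones go uncollected, or that an event not yet reached counts as a missing value rather than as censored. A condensed article may leave that to the full protocol, the case report form or the analysis plan, and the schedule figure is not shown. This stands in part: a reader might infer that later collection is ruled out, and the documents do not support that. What remains is the combination that is stated: a fixed return day, no imputation, and methods for complete times. As written, these point to omission.

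A reader might also infer that the treatment difference must shrink. That follows only when the arms differ by a shift with similar spread. The only arm-specific SDs in the document are unequal, and with them the difference widens. This objection stands, but it does not rescue the design: the bias would then flatter TEAS, and its direction would rest on unknown spreads.

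A third inference is that all the milestones suffer alike, with losses of up to half. A wider SD of 24 h would give 7.17, 5.56 and 3.55 h at control means of 84, 100 and 120 h. That SD has no source in the document, and the last case needs half the controls still without the milestone at 120 h. Nothing shows that flatus or out-of-bed times run so late.

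Nor do late patients vanish from the trial's records: adverse events are followed until the patient is stable.

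**Conclusion.** The concern holds in limited form. On the stated rules, a patient without the milestone at diary return has no usable time, and that loss depends on the outcome, so the group difference can be biased. Under equal spread, the bias is toward no difference: about 0.6 h of 8.762 h when 2% of controls are late, 1.8 h when 9% are, and 3.4 h when 25% are. With the pilot's unequal spread it can run the other way, by about 1.2 h at a control mean of 96 h.

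These sizes rest on normal times and on a difference and SDs borrowed from bowel sounds in the comparison of sham with TEAS in all phases. They illustrate the mechanism and do not estimate it. For milestones timed near 52–60 h the effect at a 120 h cut-off is negligible, so the point is mainly about solid food tolerance and late cases. Severity is low: these are secondary outcomes, and the sample size was not based on them.

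**What to change.** **Analysis.** Treat the diary milestones as time-to-event outcomes. Censor patients who have not reached the milestone at their last observation, and use Kaplan–Meier curves with a log-rank test or Cox model. If a rank test is preferred, give these patients the slowest rank in the Kruskal–Wallis test. In either case, report by arm how many had not reached each milestone at diary return, and keep them apart from patients whose diary was lost or incomplete. Recording the clock time of diary return supplies the censoring time.

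**Collection.** For patients still being recruited in Part 2, keep the diary until the last milestone or discharge.

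**Cost.** The analysis change needs only wording and no new data beyond the return time. The collection change means slightly longer diary keeping for slow patients. Its reach is limited, because Part 1 is finished and analysed and recruitment was expected to end in July 2019. For Part 1, the censored or ranked analysis can be added as a sensitivity analysis, labelled as post hoc.

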##### Postoperative nausea and vomiting

Recorded variables for this outcome include: the degree of nausea, as scored by NRS (0–10 points). This variable will be scored at 9:00 a.m. and 3:00 p.m. on days 1–5 post operation, and instances of vomiting will also be recorded. 5-HT_3_ receptor antagonists will be given for nausea scores ≥ 7 or when patients vomit ≥ 1 time.

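### The antiemetic rescue rule is stated in two incompatible ways; separately, the relative limb of the blood-pressure trigger cannot act as worded

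*Protocol article*

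**What the plan says.** **Antiemetic rescue.** The PONV paragraph of Methods/design, Interventions says that 5-HT3 "receptor antagonists will be given for nausea scores ≥ 7" "or when patients vomit more than once". The same section states that rescue pethidine and 5-HT3 "receptor antagonists will be recorded in the remedial tables". Under Secondary outcomes, Postoperative nausea and vomiting, the degree of nausea is an NRS from 0 to 10: "This variable will be scored at 9:00 a.m. and 3:00 p.m. on days 1–5 post operation, and instances of vomiting will also be recorded". That section then repeats the treatment rule with the same nausea limb but ends it "or when patients vomit ≥ 1 time".

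**Blood pressure.** The anesthesia paragraph of Interventions says: "If blood pressure falls to < 90/60 mmHg or to below 30% of baseline, 6 mg ephedrine will be administered". The heart-rate rule just before it pairs an absolute limit of 50 bpm with a relative one worded "or to 30% below baseline".

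**The concern.** Both passages on vomiting are operative treatment rules for the same drug in the same patients. They cannot both be followed for a patient with a single vomit and nausea below 7. This is a contradiction on the page, not a detail left to a fuller document.

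It matters statistically because the drug is meant to change what is measured next. Nausea is scored twice daily for five days and vomiting is recorded, so rescue after a first vomit can lower later scores and prevent a second episode. If staff in the five hospitals apply different rules, part of the variation in these secondary outcomes comes from the rule and not from TEAS. If TEAS does reduce vomiting, wider use of rescue would also tend to shrink the later differences between arms. Two readings of a rescue rule are a matter of patient care as well.

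The ephedrine wording is a different problem of the same kind: a threshold whose relative limb does nothing as written and does not match its neighbour. It bears on circulatory function, recorded under Acupuncture-balanced anesthesia efficacy.

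**Working it through.** The plan gives no figure of its own on this point, so there is none to reproduce.

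**1. The two vomiting rules as count rules.** Let V be the number of vomits, counted over the same period under both rules, and let nausea be the NRS score.

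| Patient | Interventions (V ≥ 2) | Postoperative nausea and vomiting (V ≥ 1) |
|---|---|---|
| Nausea ≥ 7, any V | rescue | rescue |
| Nausea < 7, V = 0 | none | none |
| Nausea < 7, V = 1 | **none** | **rescue** |
| Nausea < 7, V ≥ 2 | rescue | rescue |

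The rules disagree in one cell only: V = 1 with nausea below 7.

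**2. How large that cell might be.** The article gives no vomiting rate, so this is illustration only. Assume Poisson counts with mean m, so that P(V = 1) = m·exp(−m):
- m = 0.2: 0.2 × exp(−0.2) = 0.164, about 16%
- m = 0.5: 0.5 × exp(−0.5) = 0.303, about 30%
- m = 1.0: 1.0 × exp(−1.0) = 0.368, about 37%

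Each is an upper figure for its assumed m, because single vomiters with nausea of 7 or more are treated under both rules and have not been removed. The width of the range shows that the article supports no count of affected patients.

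**3. The ephedrine limb as literally worded (0.30 × baseline).** The inputs are the absolute limits of 90 and 60 mmHg.
- At an illustrative systolic baseline of 120 mmHg: 0.30 × 120 = 36 mmHg. At 200 mmHg: 0.30 × 200 = 60 mmHg. Both lie well below 90.
- The relative limb acts first only if 0.30 × baseline exceeds the absolute limit: 90 / 0.30 = 300 mmHg systolic, or 60 / 0.30 = 200 mmHg diastolic.

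**4. The same limb if it were worded like the heart-rate rule (0.70 × baseline).** It would act first above 90 / 0.70 = 128.6 mmHg systolic or 60 / 0.70 = 85.7 mmHg diastolic. At a baseline of 140 mmHg the two wordings give 0.30 × 140 = 42 and 0.70 × 140 = 98 mmHg. They therefore lead to different actions at ordinary baselines. This shows that the wording matters; it does not show which wording is right.

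**The case against.** The strongest reply is that the contradiction does little harm to the comparison. The same text governs every arm and allocation is randomised. The article says that participants, outcome assessors and analysts are blinded. Vomiting is recorded whichever rule is followed, and rescue use goes into the remedial tables. The Primary/secondary efficacy endpoints section also puts study site into the ANCOVA and stratifies the CMH test by site, which takes up part of any difference between hospitals.

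Most of this stands. A reader might infer that the nausea results will not be comparable between arms. The documents do not support that: it would need the rule to be applied differently by arm. Practitioners know the allocation, so this is possible, but no passage shows it. What the reply does not remove is inconsistency between staff within a hospital, or dilution of later scores. Recording that rescue was given also does not record which trigger was used.

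Three other inferences should be resisted. The ephedrine wording does not affect nausea; nothing links the two. Antiemetic rescue is recorded but is not listed as an outcome in the nausea and vomiting section. And a figure such as 40 to 80 of the 400 patients in each Part (10–20% × 400) would rest on an assumed rate of single vomiting. It would be an upper figure even then, and would count patients for whom the texts differ, not patients shown to have been managed differently.

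On blood pressure, it is fair to say that the 90/60 limb still works and that the neighbouring heart-rate rules suggest a slip of wording. That makes the point minor. It still has to be settled by those responsible, because the text as it stands says something else.

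**Conclusion.** The contradiction on the vomiting limb is certain and rests on no assumption: the two sections give opposite instructions for a patient with one vomit and nausea below 7. The supported consequence is inconsistent rescue between staff or centres, with added noise or dilution in the nausea scores and vomiting counts recorded afterwards. Its size cannot be fixed from the article. The primary outcome definition (bowel sounds by auscultation) and the sample size do not depend on it.

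Separately, the relative limb of the ephedrine trigger is inert at any realistic baseline, since it needs more than 300 mmHg systolic or 200 mmHg diastolic to act first, and it is inconsistent with the heart-rate wording beside it. This bears on circulatory function only.

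Both are internal inconsistencies that should be corrected. Neither undermines the trial's main comparison.

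**What to change.** 1. Reconcile the antiemetic rule in Interventions and in Postoperative nausea and vomiting into one trigger, stated once and cross-referenced. The clinical team decides which rule applies.
2. Reconcile the relative blood-pressure limb with its own 90/60 mmHg figure and with the heart-rate rule. This is also the clinical team's decision.
3. Inform all hospitals for any remaining Part 2 patients. Trial status reports Part 1 recruitment and analysis as finished, and Part 2 recruitment as due to end in July 2019, the month of publication, so few new patients may be reached.
4. Document which antiemetic rule each centre actually used in Parts 1 and 2. The recorded vomits and the remedial tables can serve as a rough check: see whether patients with one vomit and scheduled nausea scores below 7 received rescue. Report the nausea and vomiting results with that information beside them.

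Steps 1 to 3 cost a wording correction and a memo. Step 4 costs somewhat more: an inquiry to each of the five hospitals and a short tabulation of data already collected. No change to the sample size or the primary analysis is needed.
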